No interim analysis or early stopping rules are planned. The study will be monitored by an independent safety monitoring committee as outlined in section 8.0 Data and Safety Monitoring Board. The DSMB will have the right to recommend stopping the trial early if safety concerns arise. Additionally, an independent site monitor will perform periodic visits to review consent, eligibility and unanticipated adverse device effects (UADEs) for all enrolled subjects, as well as device accountability documents.

With a sample size of 32, the power to investigate subgroup effects will be limited even for large effect sizes; however, regression coefficient estimates will nevertheless be unbiased^22,23^. We will therefore explore the influence of several covariates, including gastrointestinal diagnosis, bowel length, presence/absence of colon, ileocecal valve, and stoma, as well as route of enteral nutrition administration. We will also adjust for temporary reduction or elimination of enteral nutrition due to intercurrent illness by including a yes/no indicator for any such reductions/eliminations.

### Sample Size

Historical review of patients followed by the Center for Advanced Intestinal Failure (CAIR) at Boston Children’s Hospital suggests that an average of 8 patients per year can be expected to meet the eligibility criteria, for a total of 32 subjects over 48 months. Additionally, patients currently followed by CAIR who are eligible and consent to the study will be enrolled, thus providing additional protection against attrition. Precision-based power calculations were determined with nQuery Advisor 7.0.

The primary outcome is the change in PN calories from baseline, assessed weekly at 13 assessments (study days 7, 14, 21, 28, 35, 42, 49, 56, 63, 70, 77, 84, and 90) using a baseline-adjusted time-weighted average (AUC_7-90_). It is believed that even a 10% reduction in PN calories would be clinically meaningful. In adults receiving teduglutide intended to improve enteral absorption in PN dependent patients with intestinal failure, a similar aim of 20% reduction was used to assess efficacy^24^. When this adult protocol was refined for a pediatric population, it was felt at least a 10% reduction in the volume of PN/IV support from baseline after 12 weeks of treatment was a reliable pharmacodynamic marker of increased intestinal absorptive capacity in pediatric short bowel syndrome patients who were dependent on PN/IV support. Although a 20% reduction from baseline in volume of PN/IV was used as the primary endpoint in the adult study, when adapted for a pediatric population, a ≥10% reduction was considered a valid pharmacodynamics (PD) marker of increased intestinal absorptive capacity, as agreed to by the expert clinicians with whom that study’s sponsors consulted (NPS Pharmaceuticals, Inc.). Based on the design of the teduglutide studies it was felt that the data provide similar support for a ≥10% reduction at Day 90 as a predictor of pharmacodynamic effect with the use of the RELiZORB device.

A reliable estimate for the standard deviation (SD) of AUC_7-90_ for the primary outcome in this patient population is unavailable. Unpublished data for 7 patients are available, but at least 4 of these would not meet the eligibility criteria for this study (ages 1-10; 1 had a STEP procedure; 3 have pancreatic involvement). Nevertheless, the mean±SD reduction (AUC_7-90_) for these 7 patients was 0.81±0.14, representing a 19% decrease over 90 days. Using this SD with a sample size of n=32, a 20% observed reduction in outcome would provide a 95% confidence interval (CI) = (0.75, 0.85), ruling out a true mean population reduction smaller than 15%. Conservatively, if the SD was doubled (SD=0.28), the 95% CI = (0.7, 0.9), excluding a true mean population reduction smaller than 10%, our target threshold In general, for any continuous outcome, a sample size of n=32 with two-side alpha=0.05 will provide 80% power to detect an effect size (mean/SD) as small as 0.51, considered a medium-sized effect^25^.

Dichotomous outcomes and will be presented as proportions. The variance for a proportion (p) is at a maximum, and its CI at its widest, when p=0.50. Proportions farther from 0.50 (in either direction) have smaller variances, and hence narrower CIs. A range of proportions with 95% CIs for a sample of 32 subjects is provided; small: p=0.20 (0.06 – 0.34); medium: p=0.50 (0.33 – 0.67); and large: p=0.80 (0.66 – 0.94).

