### Exploratory endpoints

- Change in 72-hour fecal fat composition and coefficient of fat absorption from enrollment, assessed at Days -3 to -1, to Days 87-89.
- Change in plasma serum fatty acid profile, and fat-soluble vitamins (A, D, E, and K) from baseline, assessed at Day 7, 14, 28, 60, and 90.
- Change in height (height-for-age z-score) and head circumference (head-circumference-for-age z-score) [in subjects < 36 months]) from baseline, assessed at Day 7, 14, 28, 60, and 90.
- Change in BMI z-score from baseline, assessed at Day 7, 14, 28, 60 and 90.
- Change in PN volume from baseline, assessed weekly.
- Change in enteral nutrition tolerance (calories and volume) from baseline, assessed weekly.
- Change in oral nutrition tolerance (calories and volume) from baseline, assessed weekly.
- Ability to wean from PN, assessed over the entire course of the study.

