### Outcomes Evaluation

Continuous outcomes, which include all outcomes except the incidence of adverse events (AEs) and incidence of weaning from PN, will be described as indicated in the general overview above using summary measures at each visit. Incidence of ever weaning from PN will be summarized by frequency count and percentage. Analysis for incidence of AEs grade 2 or higher is described in the Safety Analysis section below.

Assessment of change in continuous outcomes will be made using the area under the curve between study day 7 and 90 (AUC_7-90_), adjusted for baseline, calculated over all relevant assessment timepoints (5 and 13 post-baseline weekly assessments for measurements obtained in clinic and at home, respectively). Measurements obtained in clinic will be assessed at study days 7, 14, 28, 60 and 90, while those obtained at home will be assessed on study days 7, 14, 21, 28, 35, 42, 49, 56, 63, 70, 77, 84, 90.

Adjustment for baseline will be made by dividing the outcome value at each assessment by the baseline value, leading to interpretation of AUC_7-90_ as a mean relative percent increase or decrease in outcome depending on whether AUC_7-90_ is greater or less than unity (1), respectively. AUC_7-90_ will be calculated as a time-weighted average, given by the equation:

$$\frac{0.5\cdot\sum\left( t_{i+1}-t_{i} \right)\left( r_{i}+r_{i+1} \right)}{\sum\left( t_{i+1}-t_{i} \right)}$$

where $t_{i}$ denotes the assessment day as described above,, and $r_{i}= y_{i}/y_{1}$ denotes the outcome at assessment day $t_{i}$ divided by the baseline (day 1) value. Hypothetical examples for a single subject with reduction in outcome at each visit is shown below in Figure 3 for measurements obtained in clinic (a) and measurements obtained at home (b). The dotted lines enclose a reference AUC_7-90_=1 (indicating no change in outcome), and the gray shaded area indicates AUC_7-90_.

Figure 3. Hypothetical examples of area under the curve for one subject

| [figure not shown] | [figure not shown] |
| --- | --- |
| a. Example of in-clinic outcome assessment. | b. Example of at-home outcome assessment. |

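### The 80% power stated for every continuous outcome does not hold for head circumference, and the ratio to baseline is undefined for any child with no oral intake at baseline

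*Protocol*

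**What the plan says.** Section 10.2.5 (Sample Size) closes its discussion of continuous outcomes with a statement introduced as a general one: "for any continuous outcome, a sample size of n=32 with two-side alpha=0.05 will provide 80% power to detect an effect size" (mean/SD) of 0.51. Section 10.2.2 (Outcomes Evaluation) sets the reach of the term continuous: every outcome except adverse event incidence and weaning from PN.

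Two exploratory endpoints in section 3.3.4 fall under that definition:

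- "head circumference (head-circumference-for-age z-score) [in subjects < 36 months". The inclusion criteria in section 3.2.1 admit ages 2 to 18 years.
- "Change in oral nutrition tolerance (calories and volume) from baseline, assessed weekly".

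Section 10.2.2 also fixes how each continuous outcome is scaled: "Adjustment for baseline will be made by dividing the outcome value at each assessment by the baseline value". It gives no exception for a baseline of zero.

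**The concern.** The power sentence is universal, yet the protocol's own age limit on head circumference restricts that outcome to a one-year band of the enrolled age range. A reader who takes section 10.2.5 at its word could regard an inconclusive head-circumference result as coming from an adequately powered comparison.

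The oral-intake problem is of a different kind. All subjects are tube fed and PN dependent at entry, and no criterion requires intake by mouth. A child with no oral intake on Day 1 is therefore eligible, and the prescribed ratio cannot be formed for that child. Any such loss would be selective: a child who moves from no oral feeding to some has made an evident gain, and that gain could not enter the analysis.

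**Working it through.** **Inputs.** From section 10.2.5: n = 32, two-sided alpha 0.05, effect size d = mean/SD = 0.51, power 80%. From sections 3.2.1 and 3.3.4: ages 2 to 18 years, head circumference under 36 months only. From section 10.2.2: r_i = y_i / y_1. The protocol gives neither the number of children under 36 months nor the number with zero oral intake at baseline, so the values of n below 32 are an assumed range.

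**Formula.** For a one-sample two-sided t-test with T noncentral t, n − 1 degrees of freedom and noncentrality d√n, power = P(T > t_crit) + P(T < −t_crit).

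**The protocol's own figure.** For n = 32 the noncentrality is 0.51 × √32 = 2.885. Power is 79.8%, and the smallest d with 80% power is 0.511. The stated 80% at 0.51 is reproduced.

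**The same test with fewer analysable values.**

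| Analysable n | Power at d = 0.51 | Smallest d with 80% power |
|---|---|---|
| 32 | 79.8% | 0.51 |
| 30 | 77.0% | 0.53 |
| 24 | 66.8% | 0.60 |
| 16 | 48.0% | 0.75 |
| 8 | 23.9% | 1.16 |
| 6 | 17.6% | 1.44 |
| 4 | 11.4% | 2.13 |
| 2 | 6.2% | 11.6 |

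**Head circumference.** If ages were spread evenly over 2 to 18 years inclusive (17 one-year bands), 32/17 = 1.9, or about 2 children, would be under 36 months. If a quarter of the sample were that young, 32 × 0.25 = 8. Across 2 to 8 children, power at 0.51 is about 6% to 24%, and the smallest effect detectable with 80% power is 1.16 or more. To reach 32 values, every enrolled child would have to be aged 24 to 35 months.

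**Oral calories and volume.** With y_1 = 0 every r_i for that child is undefined, whether later intake is zero or positive. If 0, 2, 8 or 16 of the 32 children start from zero, n is 32, 30, 24 or 16 and power at 0.51 is 80%, 77%, 67% or 48%.

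**Could another rule restore the missing values?**

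- The best- and worst-case methods in section 10.2.4 fill a missing ratio from the same child's other ratios. With a zero baseline there are none.
- Section 3.4 replaces dropouts to reach 32 evaluable subjects, but it keeps anyone with at least one post-baseline assessment. Evaluability is judged per subject, not per outcome.

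**The case against.** The strongest reply is that the sentence opens with a general qualifier, is conditional on n = 32, and is correct under that condition. That stands as to the arithmetic: a reader might infer a miscalculation, and there is none. It does not rescue the scope, because the sentence names every continuous outcome and section 10.2.2 counts these two among them.

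Second, both outcomes are exploratory. Sections 10.2.1 and 10.2.2 prescribe summaries and confidence intervals with the number of subjects shown, and no test or success criterion is set for either. The sample size rests on expected recruitment and on confidence-interval width for PN calories, not on this sentence. All of that stands and keeps the point minor.

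Third, section 10.2.4 concedes limited power for subgroup effects. That remark concerns covariates such as diagnosis and bowel anatomy. It does not qualify the power statement for an outcome measured in only part of the sample.

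Fourth, a reader might infer that oral intake cannot have 32 values, or that everyone who starts eating is excluded. The protocol supports neither. It does not say that any child will have zero oral intake at baseline, and it states no rule for dropping such a child. A child with some oral intake on Day 1 has a valid ratio however much intake rises. A rule for zero denominators might also be left to a statistical analysis plan. But the protocol already fixes the ratio for all continuous outcomes, and eligibility admits baselines at which it fails.

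**Conclusion.** The point holds as a fault of scope, with a separate conditional fault in the scaling rule. For head circumference, the protocol's age limits make the stated power unattainable unless nearly all children are aged 24 to 35 months. The figure of 6% to 24% rests on an assumed 2 to 8 children, since no age distribution is given, but the direction does not depend on that assumption.

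For oral calories and volume, the ratio is undefined at a baseline that eligibility permits. The size of the loss is unknown and may be nil; the 67% and 48% figures are illustrations for assumed losses of 8 and 16 children.

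It would be wrong to conclude that the trial as a whole is underpowered or that n = 32 is unjustified. Neither the primary analysis of PN calories nor the sample size depends on this sentence.

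**What to change.** In section 10.2.5, limit the power statement to continuous outcomes with an analysable value in all 32 children, and say that head circumference will be described only, with individual values and no powered inference.

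In section 10.2.2, analyse oral calories and oral volume as absolute time-weighted change from baseline, for example in kcal/kg/day and mL/kg/day, so that a zero baseline does not remove a child. Values missing for other reasons would still be missing.

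The cost is about two sentences, a less favourable power statement for one exploratory outcome, and oral intake no longer expressed as a percent change. Visits, sample size and the primary analysis are unchanged.

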## INFORMED CONSENT AND AUTHORIZATION FOR USE AND DISCLOSURE OF PROTECTED HEALTH INFORMATION

Written informed consent and authorization of use and disclosure of protected health information must be obtained from each subject (or the subject’s legally acceptable representative) before performing any study-specific screening/baseline period evaluations. For subjects who are minors, parents and guardians are asked to document their permission to allow their children to participate in research by signing an Informed Consent Form prior to enrollment. Consents will be available in English, Spanish, Portuguese, Mandarin, and Arabic. Additional translations will be made available as needed.

One copy of the signed informed consent form and authorization for use and disclosure of protected health information form will be given to the subject, and the investigator will retain the original. The informed consent form and authorization for use and disclosure of protected health information, which is prepared by the investigator or the site, must have been reviewed and approved by the investigator’s IRB/IEC and privacy board (if separate from the IRB/IEC) before the initiation of the study. The informed consent form must contain the 20 elements of informed consent described in International Council on Harmonization E6, Section 4.8. The authorization for use and disclosure of protected health information must contain the elements required by Title 45 of the Code of Federal Regulations, Section 164.508(b) and any local regulations for valid authorizations.

## STUDY DOCUMENTATION

### Investigator Information

Investigator information is included in the study procedures manual, which is updated as needed.

### Investigator’s Study Files

Documentation about the investigator and study staff, the IRB, and the institution is required before study site initiation. Copies of these documents will be kept electronically in a BCH firewall secured SharePoint site along with the following supplemental information: a delegation of authority log, the Investigator’s Brochure, the clinical protocol and amendments, safety information, information about investigational product, information about biological samples, and information about the laboratory, the study procedures manual and study logs, CRFs*,* records of site monitoring activities, and correspondence between sponsor-investigator and the study monitor.

The sponsor-investigator will be responsible for maintaining backup of all CRF data. The investigator is responsible for maintaining backup of all electronic data systems used for primary documentation or source documentation. Electronic data will be backed up periodically. Backup records must be stored at a secure location on site, and backup and recovery logs must be maintained to facilitate data recovery.

Changes to any electronic records require an audit trail, in accordance with Title 21 of the Code of Federal Regulations, Section 11.10(e), and should indicate who made the changes, when the changes were made, and why the changes were made. An audit trail is defined as a secure, computer-generated, time-stamped electronic record that will allow reconstruction of the course of events relating to the creation, modification, and deletion of an electronic record. Audit trails must be created incrementally, in chronological order, and in a manner that does not allow new audit trail information to overwrite existing data. Finally, audit trails should be in a readable format and readily available at the site and any other location where electronic study records are maintained.

Audit trails are generated automatically for database entries. The investigator is responsible for maintaining audit trails of all electronic data systems used for source documentation.

### Case Report Forms and Source Documentation

The investigator must make study data accessible to the site monitor and the appropriate regulatory authority inspectors. The site monitor will be responsible for reviewing study documents associated with consent, eligibility unanticipated adverse device effects (UADEs), and device accountability, including CRFs, source documents and study logs.. A copy of the final CRFs will be provided to the investigator in portable document format on computer disc after study closure to be kept in the investigator’s study files.

### Retention of Study Documents

According to International Council on Harmonization E6, Section 4.9, all CRFs, as well as supporting paper and electronic source documentation and administrative records, must be retained by the investigator for a minimum of 2 years after notification that the appropriate regulatory authority has approved the product for the indication under study, notification that the entire clinical investigation will not be used in support of a marketing application, or notification that the marketing application was not approved. These documents will be retained for a longer period, however, in accordance with BCH policy for research records. If the investigator relocates, retires, or withdraws from the clinical study for any reason, all records required to be maintained for the study will be transferred to an agreed-upon designee, such as another investigator at the institution where the study was conducted.

Audit trails for electronic documents must be retained for a period at least as long as that required for the subject electronic records to which they pertain. The investigator must retain either the original of the audit trails or a certified copy of the audit trails.

## CONFIDENTIALITY

### Data

The investigator must keep all information confidential about the nature of the proposed investigation provided by the study monitor to the investigator (with the exception of information required by law or regulations to be disclosed to the IRB, the subject, or the appropriate regulatory authority).

### Subject Anonymity

The anonymity of participating subjects must be maintained. Subjects will be identified by an assigned subject number on CRFs and other documents retrieved from the site or sent to the study monitor, regulatory agencies, central laboratories, or blinded reviewers. Documents that identify the subject (e.g., the signed informed consent form) must be maintained in strict confidence by the investigator, except to the extent necessary to allow auditing by the appropriate regulatory authority, or the study monitor.

## PROTOCOL COMPLIANCE

Substantive changes in the protocol include changes that affect the safety of subjects or changes that alter the scope of the investigation, the scientific quality of the study, the experimental design, dosages, assessment variable(s), the number of subjects treated, or the subject-selection criteria. Such changes must be prepared as a protocol amendment by the sponsor-investigator. A protocol amendment must receive IRB approval before implementation. In parallel with the IRB approval process, the protocol amendment will be submitted to the appropriate regulatory authority as an amendment to the regulatory submission under which the study is being conducted. If a protocol amendment requires changes in the informed consent form, the revised informed consent form prepared by the investigator must also be approved by the IRB before implementation.

Departures from the protocol are allowed only in situations that eliminate an immediate risk to a subject and that are deemed crucial for the safety and well‑being of that subject. The investigator or the attending physician also will contact the IRB as soon as possible in the case of such a departure. These departures do not require preapproval by the IRB; however, the IRB must be notified in writing as soon as possible after the departure has been made. In addition, the investigator will document in the subject’s CRF the reasons for the protocol deviation and the ensuing events.

## STUDY MONITOR FUNCTIONS AND RESPONSIBILITY

The study monitor, in accordance with the sponsor-investigator’s requirements, will ensure that the clinical study is conducted and documented properly by carrying out the activities outlined in International Council on Harmonization E6, Section 5.18.4. The study monitor will perform periodic visits to review consent, eligibility and unanticipated adverse device effects (UADEs) for all enrolled subjects, as well as device accountability documents.

## GENERAL INFORMATION

The investigator will refer to the study procedures manual, and any other information provided about this investigational product and details of the procedures to be followed during the conduct of this clinical study.

